## Abstract

**Background:**

Total joint arthroplasty (TJA) is among the most common elective surgeries performed in the United States, and recent advances in perioperative care have shortened hospital stays and streamlined recovery. Yet, even brief periods of mechanical ventilation and anesthesia measurably weaken respiratory muscle function in the early postoperative period. Preoperative inspiratory strength training (IST) has been shown to reduce postoperative pulmonary complications in patients undergoing major cardiothoracic surgery, but whether these benefits extend to shorter procedures such as TJA, where hospital stays are already brief, remains unknown.

**Objective:**

This study aims to investigate whether preoperative IST prior to TJA surgery alters respiratory strength, lung function, and functional mobility. We hypothesize that preoperative IST is feasible and effective in increasing inspiratory strength and promoting the return of early postoperative respiratory function and functional mobility before hospital discharge.

**Methods:**

The study hypothesis will be tested using a randomized, prospective design at a single urban academic health system. Adults scheduled for TJA surgery will be randomized to either undergo daily IST (dIST), complete an acute IST (aIST) session in the preoperative area, or receive clinical standard of care (SOC). Inspiratory muscle strength and pulmonary function will be evaluated upon enrollment at a baseline assessment approximately 4 weeks before surgery and will be repeated on the day of surgery. Postoperative changes will be evaluated through the first 24 hours across 3 aims: to evaluate the feasibility and effectiveness of dIST for increasing preoperative respiratory strength (aim 1), to compare the effects of dIST and aIST on postoperative respiratory strength measures and lung function (aim 2), and to evaluate 24-hour functional outcomes (aim 3).

**Results:**

The study was funded in September 2023 and received institutional review board and safety officer approvals in December 2023. Enrollment began in March 2024, and as of May 2026, a total of 31 participants have been enrolled. Data analysis and publication of primary results are expected in 2027.

**Conclusions:**

This trial will provide the first controlled investigation of preoperative IST in TJA, offering early evidence on whether a low-cost, nonpharmacological intervention can preserve respiratory strength and accelerate functional recovery in this high-volume surgical population.

## Introduction

Total joint arthroplasty (TJA) surgeries are common elective surgeries that result in more than 1.3 million hospital stays in the United States annually [1], and surgical volume is expected to continue to grow through 2040 [2]. In the years since TJA surgeries transitioned away from being inpatient-only procedures, the hospital length of stay for TJA has progressively declined, and the prevalence of outpatient procedures has expanded [3]. In conjunction, clinical readiness for TJA has evolved to include optimizing preoperative education, implementing multimodal anesthesia and pain management, and initiating early lower extremity strengthening and walking rehabilitation [4-7]. However, an underappreciated aspect of TJA readiness and recovery is the potential impact of surgery on respiratory muscle capacity.

The primary inspiratory muscle, the diaphragm, undergoes acute remodeling in response to changes in activity (reviewed by Fogarty et al [8]). Hospital clinical practices such as mechanical ventilation, sedation, and anesthesia significantly decrease diaphragm recruitment, which can degrade ventilation and important related behaviors such as coughing [9]. Importantly, even short periods of mechanical ventilation typical of TJA surgeries contribute to impaired inspiratory force generation [10]. Lung volumes fall after TJA surgery and remain depressed 24 hours later [11]. The extent of the decline is most closely associated with older age [12], and acutely decreased lung function subsequently increases the risk for pulmonary complications [13].

Although postoperative pulmonary complications (PPCs) are relatively uncommon after TJA [14], they prolong the hospital stay, increase costs, and increase the mortality risk [14]. Older adults and those with preexisting lung disease and medical comorbidities may be more susceptible to respiratory weakness, poor cough function, and impaired oxygenation, which can interfere with postoperative rehabilitation and extend the projected length of stay [15,16]. In addition to patients with multiple preexisting health issues, people from racial and ethnic minority groups or those with low socioeconomic status also experience higher risks for acute complications after TJA [17-19]. Therapies designed to limit postoperative respiratory decline have the potential to address unmet needs and improve TJA outcomes for these underserved individuals.

Controlled studies in other surgical populations reveal significant clinical benefits of preoperative inspiratory strength training (IST) compared to usual surgical care. IST for 2-4 weeks before surgery significantly strengthens the respiratory muscles [20-24], mitigates surgical declines in lung function, and lowers the incidence of PPCs [22-26]. Additionally, strength gains associated with preoperative IST are associated with shorter lengths of stay [22,23], which may potentially reduce costs [23]. Although preoperative IST for cardiothoracic surgery is not in itself novel, its impacts on orthopedic surgeries are scarcely studied. We postulate that preoperative IST may be a powerful tool to preserve respiratory strength and cough force in people undergoing TJA. Aim 1 of this study is to investigate the effect of daily IST (dIST), delivered at high intensity preoperatively, on increasing respiratory strength and lung function before TJA.

Although preventative care and educational approaches are 2 recommended strategies to improve health [27], people from underserved communities may lack access to the resources necessary to attend appointments or struggle to complete unsupervised training. Lack of transportation, social support, and health literacy can impede regular adherence to a preoperative exercise plan [28]. As single intense inspiratory loading bouts transiently increase inspiratory pressure generation [29] and enhance central excitability [30], we postulate that they have the potential to counter the downregulation of respiratory neural drive during brief periods of mechanical ventilation. Thus, aim 2 of this study will evaluate whether short-term potentiation of inspiratory drive from a single acute IST (aIST) session immediately prior to surgery can attenuate postoperative declines in inspiratory pressure generation. As high-intensity IST programs that increase maximal inspiratory pressure (MIP) can enhance diaphragm fatigue resistance and reduce exercise-induced dyspnea [31,32], aim 3 of this study will evaluate whether either IST approach can improve functional mobility and dyspnea during the 24-hour postoperative rehabilitation session.

## Methods

### Trial Design

This is a randomized, prospective, single-blind clinical study. Eligible participants will be randomized to one of three study groups: (1) dIST, consisting of IST 5 days per week for a period of 2 to 4 weeks before surgery; (2) aIST, consisting of a single aIST session delivered just prior to surgery; or (3) standard of care (SOC), consisting of usual preoperative, surgical, and postoperative care. Participants will be tested at established time points beginning with a baseline preoperative visit approximately 1 month before surgery and will participate in tests through 24 hours following surgery. PPCs will be monitored for 30 days. This study is registered on ClinicalTrials.gov (NCT5381818), and trial reporting will be guided by the SPIRIT (Standard Protocol Items: Recommendations for Interventional Trials; Checklist 1) and CONSORT (Consolidated Standards of Reporting Trials; Checklist 2) procedures (Figure 1) [33]. Proof-of-concept data were collected with support from an internal pilot grant award, and the controlled study is being conducted with funding from the National Institute on Aging (NIA; R21 AG083667).

The study will take place at a single academic health care system in the urban United States (Figure 2). Screening procedures will occur in the outpatient clinic, and preoperative and postoperative procedures will be conducted in the hospital setting. MIP, forced vital capacity (FVC), and the 6-minute walk distance (6MWD) test will be assessed at baseline during an initial outpatient assessment visit prior to total joint replacement (typically approximately 4-6 weeks before surgery and, when possible, timed to coincide with the preoperative “total joint education” clinical session). MIP and FVC will then be repeated on the day of surgery and 24 hours after extubation. The research team will track pulmonary complications based on the European Perioperative Clinical Outcomes (EPCO) definitions. Additionally, we will record clinical physical therapy (PT) documentation of participant vital signs, dyspnea, functional status (Activity Measure for Post-Acute Care [AM-PAC] “6-Clicks” mobility score, standard clinical care), and dyspnea and walking distance at the 24-hour PT session. Diaphragm ultrasound is an exploratory outcome measure that will be assessed in preoperative holding and 24 hours postoperatively. Participant confidentiality will be protected by assigning a unique study number to each participant and using the participant number for data collection. Data will be entered and stored in a REDCap (Vanderbilt University) database on a secure institutional drive.

**Figure 1. F1:**
[figure not shown]
Projected flowchart of the clinical trial. aIST: acute inspiratory strength training; dIST: daily inspiratory strength training; IST: inspiratory strength training; PT: physical therapy; SOC: standard of care; TJA: total joint arthroplasty.

**Figure 2. F2:**
[figure not shown]
Outline of testing sessions and intervention groups. Participants will be randomized to 1 of 3 groups: daily inspiratory strength training (dIST) for 2-4 weeks before total joint arthroplasty, a single acute inspiratory strength training (aIST) session in the preoperative holding area, or standard of care (SOC; no training). Testing will occur upon enrollment, in the preoperative area, and 24 hours postoperatively. IST: inspiratory strength training.

### Participant Recruitment and Screening

Individuals with physician approval for elective joint replacement surgery who are interested in research participation will be referred to the study team by the Department of Orthopedics. We will enroll up to 60 participants. This includes 30% (18/60) participants who participated in nonrandomized, proof-of-principle pilot work for the purpose of estimating the sample size for the randomized study. Up to 70% (42/60) additional participants will be randomized, with the goal of completing procedures in 60% (36/60) randomized participants. The inclusion criteria are outlined in Textbox 1. Patients who meet the eligibility criteria and agree to participate in the study will sign a University of Florida Institutional Review Board (IRB)–approved informed consent form. The study coordinators will screen patients according to the inclusion and exclusion criteria via participant interview and medical record review.

Textbox 1.Inclusion and exclusion criteria for study participation.
**Inclusion criteria:**
Aged 55 to 85 years at enrollmentScheduled for lower extremity joint arthroplasty surgery with a projected surgical time of >1 hourAble to follow instructions to complete inspiratory exercisesAble to communicate adverse effects or a need for assistanceOne or more of the following risk factors for postoperative pulmonary complications:Previous or current smokingDiagnosis of pulmonary diseaseDyspnea with minimal exertion (ascending 1 flight of stairs)Modified Frailty Index-5 score of ≥2Impaired lung function (forced expiratory volume in 1 second and/or forced vital capacity <80% predicted)Respiratory muscle strength below the lower limit of normal for age and sex
**Exclusion criteria:**
American Society of Anesthesiologists physical status classification of ≥4Acute use of corticosteroids or antibiotics within the past 2 weeksPreoperative dependence on continuous supplemental oxygenPreoperative dependence on positive pressure breathing support while awake and upright (nighttime continuous positive airway pressure permitted)Progressive neuromuscular diseaseParticipation in a pulmonary rehabilitation programGlobal Initiative for Chronic Obstructive Lung Disease classification ≥3, indicating severe obstructive pulmonary diseaseActive infectious disease requiring isolation (eg, COVID-19)

### Randomization and Blinding

Consenting patients who meet the inclusion criteria will be randomized to a study group according to a randomization sequence created using SAS (version 9.4; SAS Institute Inc). Due to the nature of the intervention, participants and the coinvestigator assigned to conducting the intervention will be aware of the group assignment. Surgeons and study evaluators will remain blinded to group assignment.

### Inspiratory Training Interventions

Participants will be randomized to the dIST, aIST, or SOC group.

#### dIST

The dIST group will complete preoperative IST for approximately 2 to 4 weeks before surgery. Participants will be given a portable device (EMST75/IA150, Aspire Products LLC) containing an adjustable-tension spring to provide a pressure-threshold training load. Participants will complete 5 sets of 5 maximal inspiratory breaths at maximal volume and speed, resting for approximately 1 minute between sets. A nasal clip will reduce pressure loss through the nose. The dIST training intensity will be 70% of the participant’s MIP, and the intensity will not be progressed further. The coinvestigator conducting the training will teach participants to use the IST device, complete the exercises, and record their work on a training log. The coinvestigator will call the patient at the first home IST session and weekly thereafter to address any questions that arise.

#### aIST

The aIST group will complete a single session of preoperative IST within 30 minutes prior to anesthesia induction, using a pressure-threshold training device (EMST75/IA150). Participants will complete 5 sets of 5 maximal inspiratory breaths at maximal volume and speed, with approximately 1 minute between sets. A nasal clip will be used to reduce pressure loss through the nose. The aIST target training intensity will be 70% of the participant’s MIP.

#### SOC

The SOC group will serve as the control group and will receive usual preoperative, surgical, and postoperative care. This includes the preoperative TJA class sponsored by the Department of Orthopedics, preoperative lower extremity strengthening home exercises, provision of an assistive device, and counseling for smokers to quit smoking preoperatively.

### Outcomes

#### Respiratory and Functional Assessments

A study evaluator blinded to group assignment will be responsible for conducting the assessments. All intervention groups will complete study assessments.

##### MIP

MIP is the primary outcome measure and represents the most negative pressure achieved by a participant during a maximal static inspiratory effort. Participants will be tested in accordance with American Thoracic Society (ATS) guidelines. MIP will be tested at the baseline assessment (approximately 4 weeks before surgery), in preoperative holding, and 24 hours postoperatively. Trials will be administered until a 10% variability is achieved across 3 trials (usually within 5 trials).

##### Spirometry

Spirometry is a secondary outcome measure. Test maneuvers will follow ATS guidelines [34] and shall include (1) FVC, the volume of air a person can forcefully and quickly exhale after taking a maximal inhalation; (2) forced expiratory volume in 1 second (FEV1), the volume of air forcefully exhaled during the first second of an FVC maneuver; (3) inspiratory capacity (IC), the volume of air inspired from end-expiration to total lung capacity; and (4) peak cough flow (PCF), the maximum airflow generated during a voluntary cough. Participants will be tested at the baseline assessment, in preoperative holding, and 24 hours postoperatively.

##### 6MWD

6MWD is a secondary outcome measure and represents the maximal distance walked by the patient during the 24-hour postoperative PT session, using the assistive device determined by the physical therapist to be most compatible with the patient’s underlying physical status and postoperative condition (pain and weight-bearing restrictions). In addition to the distance walked, the patient-reported primary limitation (eg, joint pain, weakness, or dyspnea), peak dyspnea level using the modified Borg scale [35], and vital signs will be recorded.

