##### AM-PAC “6-Clicks” Functional Mobility

The 6-Clicks is a secondary outcome measure and assesses the difficulty or level of assistance needed for bed mobility, sit-to-stand, supine-to-sit, seated transfers, walking, and ascending stairs; scores are predictive of discharge needs after total knee and hip arthroplasty [36]. The 6-Clicks score is part of standard clinical care and will be recorded from the electronic health record at the 24-hour PT session.

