#### Statistical Analysis

To test whether dIST or even a single aIST session can accelerate postoperative respiratory and functional recovery, the primary analysis will compare between-group changes using a mixed-effects model to account for within-subject correlation in repeated measurements. Fixed main effects will include intervention and time; the participant will be included as the random effect. If baseline measures differ between groups, an analysis of covariance (ANCOVA) will be used. The primary analyses will be (1) change in MIP for dIST (vs other groups) from baseline to the preoperative assessment and (2) change in MIP from the preoperative assessment to the postoperative assessment for dIST and aIST (vs SOC). Holm adjustments will be applied for multiple comparisons.

Feasibility will be characterized by the percentage of completed dIST sessions, diary completion, and attrition rate. These will be reported as descriptive variables. The prevalence of PPCs will be compared between groups using chi-square or Fisher exact tests, as appropriate.

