The primary outcome of this trial is MIP, a clinical estimate of strength. However, additional secondary measures were included to investigate the effects of the interventions on early postoperative activity-based measures such as coughing force, walking distance, and functional mobility, along with patient-reported dyspnea. Postoperative walking and functional mobility are important functional limitations following TJA that influence the timing of disposition and postacute rehabilitation needs [40]. Although the projected effect size of preoperative IST appears robust for impairment-level outcomes, this study will also provide early indication of its ability to carry over to functional activities and participation-level recovery. As preoperative 6MWD can predict functional ambulation after total joint surgeries [41], the statistical plan will explore preoperative walking distance as a covariate.

As a first preliminary study in TJA, some aspects of the study design remain limited. The sample size was projected from published work in cardiac surgery to detect changes in MIP between dIST and no preoperative exercise. Although we anticipate gaining valuable feasibility information regarding completion of aIST in the acute preoperative setting, we may lack the power to comprehensively distinguish which preoperative training approach (dIST or a single aIST session) can more effectively retain postoperative MIP and functional mobility. Postoperative walking and functional mobility at 24 hours can be influenced by a multitude of factors beyond respiratory strength and may include variations in pain management and pain perception, the ability to participate in same-day therapy, and lack of sleep, nutrition, or hydration. Blinded evaluators will plan for premedication with nursing before the planned 24-hour PT session and ensure that the timing does not interfere with meals. Participants randomized to SOC did not receive a respiratory trainer or training diary or undergo weekly check-ins, and the absence of a sham or attentional control group could inadvertently introduce expectation bias. Even in higher-risk patients, there may be few PPCs in the 30-day period following TJA. However, monitoring complications will enable us to further explore the prevalence of postoperative pulmonary issues in this cohort. Surgeons and study evaluators will be blinded to group assignment, but patients and other study staff will, by necessity, know the allocation.

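### The repeated-measures change model is introduced for functional recovery, but 6-Clicks is measured once, the 24-hour walk is not defined as the baseline test, and adjustment for preoperative walking is left to the data

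*Protocol article*

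**What the plan says.** All places are in the protocol article.

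- **Model.** Statistical Analysis gives its purpose as testing whether training can "accelerate postoperative respiratory and functional recovery". To that end, "the primary analysis will compare between-group changes using a mixed-effects model to account for within-subject correlation in repeated measurements". The terms are: "Fixed main effects will include intervention and time; the participant will be included as the random effect". On baseline: "If baseline measures differ between groups, an analysis of covariance (ANCOVA) will be used". The two primary analyses then listed are both changes in MIP. Chi-square or Fisher tests are reserved for pulmonary complications.
- **6-Clicks.** A secondary outcome that "will be recorded from the electronic health record at the 24-hour PT session". No other time is given in its own section, in Trial Design or in Feasibility and Safety Assessments.
- **Walking at baseline.** Trial Design says "the 6-minute walk distance (6MWD) test will be assessed at baseline during an initial outpatient assessment visit". It then lists only MIP and FVC as repeated.
- **Walking at 24 hours.** The 6MWD section says the secondary outcome "represents the maximal distance walked by the patient during the 24-hour postoperative PT session", with an assistive device chosen by the therapist. It mentions neither a six-minute limit nor a baseline test. Trial Design and Feasibility and Safety Assessments call the 24-hour measure simply walking distance, taken from clinical physical therapy records.
- **Covariate.** The Discussion cites evidence that preoperative 6MWD predicts ambulation after joint surgery, and says that "the statistical plan will explore preoperative walking distance as a covariate".

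**The concern.** Aim 3 concerns function at 24 hours. The only between-group model that the article introduces for functional recovery is built for outcomes with several measurements per participant. 6-Clicks has one. Walking has two measurements under one label, and the text does not establish that they are the same test.

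The one preoperative functional measure, which the authors themselves treat as prognostic, has no fixed role. It is to be explored, and the general rule brings in ANCOVA only when groups are seen to differ at baseline. In a randomized trial an observed baseline difference is a chance event. The reason to adjust is that the covariate predicts the outcome, and that is known in advance. A choice made after looking gives more than one possible aim 3 result and may forgo precision, which matters with a target of 12 completers per group.

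**Working it through.** **1. The plan's own figure, and what it covers.** Sample Size Projection gives 36 participants, 12 per group, a 3×3 group-by-time interaction, partial η² = 0.06, f = 0.253, α = 0.05 and power 0.83.

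- f = √(0.06/0.94) = 0.2526, which agrees.
- Noncentrality λ = f²·N·m/(1−ρ), with N = 36, m = 3 times and ρ = 0.5. The article gives no ρ, so 0.5 is an assumption.
- λ = 0.253² × 36 × 3 / 0.5 = 13.83; df = (3−1)(3−1) = 4 and (36−3)(3−1) = 66; sphericity assumed.
- Power = 0.833, so 0.83 is reproduced. With other values of ρ it would be 0.50 (ρ = 0), 0.67 (0.3) or 0.97 (0.7).

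The figure belongs to an outcome measured three times, as MIP is. It says nothing about an outcome measured once.

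**2. Measurement times against model terms.**

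| Outcome | Baseline | Day of surgery | 24 h | Can the change model be fitted? |
|---|---|---|---|---|
| MIP | yes | yes | yes | yes |
| Spirometry | yes | yes | yes | yes |
| 6-Clicks | no | no | yes | no |
| Walking | 6-minute test | no | PT-session distance, limit not stated | only if both are the same test |

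With one value per participant there is no time effect, no group-by-time term and no change, and the participant variance cannot be separated from residual error. For 6-Clicks the ANCOVA fallback has no baseline value of the same score to use. For walking, a change would subtract a six-minute distance from a session distance of unstated duration. As a covariate, by contrast, the baseline test need not be the same quantity as the outcome.

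**3. What a single-time comparison can detect with 36 participants.**

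- Three groups, one-way ANOVA, df 2 and 33, λ = 0.253² × 36 = 2.30: power is about 0.24. For 80% power f must be about 0.54. This f describes group means at one time and is not the same quantity as the interaction f, so the figure is an illustration only.
- Two groups of 12, two-sided 0.05, 80% power, no Holm adjustment: minimum detectable difference 1.20 SD.

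**4. What prespecified adjustment for preoperative 6MWD could add.** The residual variance factor is 1−r², where r is the correlation of preoperative 6MWD with the 24-hour walk. The article gives no r, so a range is shown. The comparison is with no adjustment.

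| Assumed r | 1−r² | Variance removed | 1/(1−r²) | Detectable difference, 12 v 12 |
|---|---|---|---|---|
| 0.3 | 0.91 | 9% | 1.10 | 1.14 SD |
| 0.4 | 0.84 | 16% | 1.19 | not computed |
| 0.5 | 0.75 | 25% | 1.33 | 1.04 SD |
| 0.6 | 0.64 | 36% | 1.56 | 0.96 SD |

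For r from 0.4 to 0.6 the gain is equivalent to about 19% to 56% more participants. The last column allows one degree of freedom for the covariate.

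**The case against.** The strongest reply is that the change model was never meant for these outcomes. Statistical Analysis calls it the primary analysis and then names only MIP changes. 6-Clicks and walking are secondary, the Abstract states aim 3 as outcomes at 24 hours, and a condensed article may leave their model to an analysis plan that is not shown. Much of this stands. A reader might infer that the aim 3 analysis is not estimable or not interpretable. The article does not support that: a plain group comparison at 24 hours is possible, and a separate plan may specify it. What remains is that the model's stated purpose expressly includes functional recovery, so the article sets a scope that the model cannot cover.

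A reader might also infer that a baseline-to-24-hour walking difference is planned. No section says so; only MIP and FVC are listed in Trial Design as repeated, and the Discussion gives preoperative walking the role of a covariate. Nor is it shown that the two walks are different tests. The label 6MWD suggests that a timed test within the therapy session may be intended, and a therapist-chosen device does not by itself change the quantity. The definition is unresolved rather than demonstrably wrong.

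On the covariate, exploring states no selection rule, so it goes too far to say that it will be used only if it helps. The gain in precision also rests on an assumed correlation and on comparison with no adjustment, which the article does not promise either. It remains true that the article fixes no adjustment and ties ANCOVA to observed baseline differences.

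**Conclusion.** The point holds as a matter of scope, definition and prespecification for secondary outcomes. The change model cannot be fitted to 6-Clicks and does not suit walking as now described. The sections on walking must be reconciled. Adjustment for preoperative 6MWD is left to the data, although the authors cite it as prognostic.

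The effect on precision is moderate and conditional: 16% to 36% less residual variance if r is 0.4 to 0.6, and only 9% if r is 0.3. The wording and definition points carry no number. The two primary MIP analyses are untouched, as is the stated power of 0.83, which reproduces at an assumed within-participant correlation of 0.5.

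**What to change.** 1. Reconcile Trial Design, the 6MWD section and Feasibility and Safety Assessments on what is walked at 24 hours. State whether it is timed, and give the outcome its own name, distinct from the baseline 6MWD.
2. State in Statistical Analysis that the mixed model of change applies only to outcomes measured repeatedly, namely MIP and spirometry.
3. Analyse 24-hour walking distance by ANCOVA, with preoperative 6MWD as a prespecified covariate whether or not the groups differ at baseline. Replace the wording on exploring it in the Discussion accordingly.
4. Compare 6-Clicks between groups as a single 24-hour outcome, by a method suited to an ordinal score. A proportional-odds model or a rank-based comparison would serve; the choice between them is secondary.

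The article already plans to collect all of these variables. The cost is a wording change and about one degree of freedom in the walking analysis. The article expects data analysis and publication in 2027, so the choice can be fixed before the results are seen.
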